Therefore, the primary goal of the TEAMS (TElerehabilitation And Multiple Sclerosis) is to implement a single-blind, RCT designed to compare the effectiveness of an 8-week home-based telerehab VR program with conventional therapy in PwMS with manual dexterity difficulties. Secondary aims include (a) evaluating the impact of the programs on quality of life after the intervention and follow-up 1 month later and (b) evaluating the impact of the programs on adherence and satisfaction. A tertiary aim will be to generate effect sizes which can be used to power a larger clinical trial aimed at improving upper limb functional activities via telerehab in PwMS in Italy and Israel. We hypothesize that there will be no difference in outcomes between a home-based telerehab VR training program aimed at improving functional activities of the upper limbs compared with a conventional clinic-based program after the intervention and follow-up 1 month later. We also intend to corroborate a secondary hypothesis that performing the telerehab VR training will lead to better outcomes in quality of life and adherence to upper limb exercise.

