#### Sample size

The sample size is based on Julious’s [31] recommendation that the rule of thumb for a pilot study is a sample size of 12 subjects per group. The justifications for this sample size are based on rationale relating to feasibility, mean and variance precision, regulatory considerations, and the expected change in the study’s primary outcome measure (NHPT). According to the literature, a 20% change in the NHPT demonstrates a clinically meaningful worsening in PwMS [32]. In our study, power will be set at 80% and alpha at 5%. Therefore, 24 subjects (12 in each group) will be required in order to detect differences between the two treatment groups (assuming non-inferiority with moderate correlations among covariates, *r*-squared = 0.50).

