### Outcomes

#### Primary outcomes (collected at T0, T1, T2)

##### NHPT

The NHPT was selected based on the widespread adoption and extensive data available. Furthermore, the NHPT is recommended as a gold standard for measuring manual dexterity in PwMS [32]. The NHPT has excellent psychometric properties as to reliability, discriminant, concurrent, and ecological validity; can detect progression over time; is sensitive to treatment; and, as such, is recommended for inclusion in clinical trials. Briefly explained, the NHPT requires participants to repeatedly place nine pegs into nine holes, one at a time, as quickly as possible and then remove them from the holes. The total time needed to complete the task is then recorded. Two consecutive trials with the dominant hand are immediately followed by two consecutive trials with the non-dominant hand [4, 8].

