#### Secondary outcomes (collected at T0, T1, T2)

##### Action Research Arm Test (ARAT)

The ARAT is a 19-item observational measure used by physical therapists and healthcare professionals to assess upper extremity performance in terms of coordination, dexterity, and functioning in several neurologic conditions, including MS [36]. Items comprising the ARAT are categorized into four subscales (grasp, grip, pinch, and gross movement) and arranged in order of decreasing difficulty, with the most difficult task examined first, followed by the least difficult task. Task performance is rated on a 4-point scale, ranging from 0 (no movement) to 3 (movement performed normally).

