### Statistical analysis

Data analysis will be performed by the SPSS 25.0 program. The data will be initially examined for normality violations, outliers, errors, and patterns of missing values; missing data will be replaced by multiple imputation techniques found in the SPSS. In the event of exacerbations, the analysis will be conducted with and without the individuals who had relapsed in order to identify any untoward effects on the outcomes. The data analysis itself will follow intent-to-treat principles. The effect of the intervention on the NHPT (aim 1), ARAT (aim 1), MAM-36 (aim 1), SF-36 (aim 2), and adherence and user satisfaction (aim 3) will be examined using the Condition × Time mixed model multivariate analysis of variance (MANOVA) followed by an inspection of the univariate F-ratios. Conditions will be a between-subjects factor and time and a within-subjects factor. Interactions and main effects will be further calculated using post hoc analyses with a correction of alpha. Effect sizes associated with univariate *F*-statistics will be expressed as eta-squared (*η*^2^), and effect sizes based on a difference in mean scores will be expressed as Cohen’s *d*. We will include cognitive scores (BRB-N) as covariates in all final statistical analyses.

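### NHPT is the only primary outcome, but the analysis ties NHPT, ARAT and MAM-36 equally to aim 1 and does not say that NHPT decides it

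*Protocol article*

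**What the plan says.** The protocol article ranks its outcomes clearly in two places. The Sample size section refers to a single "primary outcome measure (NHPT". In the Outcomes section, the NHPT is the only measure under the heading "Primary outcomes (collected at T0, T1, T2", while ARAT and MAM-36 stand under "Secondary outcomes (collected at T0, T1, T2".

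The Statistical analysis section does not carry that ranking forward. It names the NHPT for aim 1 and, with the same tag, "ARAT (aim 1), MAM-36 (aim 1", then SF-36 for aim 2 and adherence and satisfaction for aim 3, all within one Condition × Time MANOVA whose univariate F-ratios are then examined. A correction of alpha is mentioned for the post hoc work on interactions and main effects; neither the method nor the family of tests is named.

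Two further statements bear on what an NHPT result would be. The test is taken in both hands: "Two consecutive trials with the dominant hand are immediately followed by two consecutive trials with the non-dominant hand". The main hypothesis in the Background, that the programmes do not differ, applies "after the intervention and follow-up 1 month later", so it spans both T1 and T2.

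**The concern.** A reader who follows the Statistical analysis section exactly ends with three F-ratios of equal standing for the primary aim. If NHPT and ARAT disagree, the section does not say whether aim 1 has been answered, or how. The outcome sections imply that the NHPT settles it; the analysis section does not.

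This matters in both directions. A difference could be reported on whichever of the three shows one. Comparability, which the authors expect and which the Discussion turns into advice that patients may choose either programme, could be claimed on whichever measure agrees. The Discussion speaks of upper limb outcomes in the plural, which does not help.

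**Working it through.** **Inputs (all from the protocol article)**
- Primary outcome: NHPT alone (Sample size; Outcomes).
- Outcomes tagged aim 1: NHPT, ARAT, MAM-36 (Statistical analysis).
- Alpha 5%, power 80%, R-squared 0.50, 12 per group (Sample size). Sidedness, SD and non-inferiority margin are not given.
- Hands tested on the NHPT: two (Outcomes, NHPT).
- Assumed here, not in the article: the correlation between test statistics.

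**The plan's own figure.** The total of 24 is 2 × 12, and 12 per group is the cited pilot rule of thumb. The power statement cannot be reproduced without an SD and a margin. What can be shown, taking two-sided 5%, is the difference that 12 per group would detect on one outcome in one test:

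(1.960 + 0.842) × √(2/12) × √(1 − 0.50) = 2.802 × 0.408 × 0.707 = 0.81 SD.

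The size is thus argued for a single NHPT comparison.

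**Counting the aim-1 tests.** T0, T1 and T2 enter one Condition × Time test per outcome, so visits do not multiply the count at the F-ratio stage. There are 3 F-tests, or 4 if the NHPT is analysed separately in each hand (2 NHPT + 1 ARAT + 1 MAM-36).

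**Chance of at least one false difference, each test at 5%**
- Independent, 3 tests: 1 − 0.95³ = 1 − 0.8574 = 14.3%.
- Independent, 4 tests: 1 − 0.95⁴ = 1 − 0.8145 = 18.5%.
- Equally correlated normal test statistics, by simulation (200,000 draws):

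| Assumed correlation | 3 tests | 4 tests |
|---|---|---|
| 0.3 | 13.7% | 17.5% |
| 0.5 | 12.6% | 15.6% |
| 0.7 | 11.0% | 13.0% |
| 0.9 | 8.3% | 9.4% |

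Even at 0.9 the rate stays above 5%.

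**The no-difference direction.** The article gives no margin, so this can be sized only under a condition. If any one of three independent 5%-level non-inferiority tests could count, and every true difference sat at its margin, the chance of at least one false claim would again be 1 − 0.95³ = 14.3%.

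**Splitting alpha instead.** Suppose one test at 12 per group had exactly 80% power. Bonferroni over three gives a critical value of 2.394 (two-sided 0.05/3), and power per test becomes Φ(2.802 − 2.394) = Φ(0.408) ≈ 66%. Restoring 80% would take 17 per group. The planned size therefore suits one deciding result better than three that share alpha.

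**The case against.** The strongest reply is that an aim is not an outcome rank. The tags may simply map instruments to topics: three upper-limb measures to aim 1, quality of life to aim 2. A primary aim may properly have one primary outcome and supporting secondary ones, the outcome headings already fix that rank, and the analysis section never calls ARAT or MAM-36 primary. The MANOVA also comes before the F-ratios and could act as a screen. Finally, this is a 24-person pilot that also aims to generate effect sizes.

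Part of this stands. The conflict is one of unranked roles, not an explicit relabelling, and pilot status softens the consequence. But the analysis section is where the deciding result should be identifiable, and it gives all three the same standing. It does not make the MANOVA a condition for reading the F-ratios, and the same sentence also covers SF-36, adherence and satisfaction, so an omnibus result would not isolate aim 1. The article also claims 80% power and promises practical conclusions, which invites a confirmatory reading.

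Two stronger readings are tempting and not supported:
- A reader might multiply outcomes by the two follow-up visits and both hands, reach six or eight uncorrected tests, and quote a larger error rate. Time is a factor within each test, and visit contrasts belong to the post hoc stage, where a correction is stated.
- A reader might infer that patients qualify on one hand only, so that pooling hands hides differences. The Inclusion criteria do not say which hand the peg-test cut-off applies to. How trials and hands are combined can properly be left to an analysis plan, so its absence from the article is not itself a fault.

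**Conclusion.** The point holds as an inconsistency in the article's own text: one primary outcome by heading and sample size, three unranked outcomes for the primary aim in the analysis. Because the article itself states both, this is not just detail awaiting an unseen analysis plan.

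If any of the three F-ratios may serve as the answer, the chance of at least one false difference is about 14% (independent) or about 13% (assumed correlation 0.5), rising to 18.5% (independent) if the NHPT is tested in each hand, against a nominal 5%. This rests on each F-ratio being read at 5% without correction; the article does not say that they are corrected.

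A reader might take 14% as the chance of wrongly declaring the trial's hypothesis confirmed. That does not follow: the hypothesis is no difference, so a false difference counts against it. For that hypothesis the defect is that no outcome is named on which comparability will be judged, and without a margin it can be sized only under the condition given above.

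**What to change.** In the Statistical analysis section, state that aim 1 is decided by one prespecified between-group comparison of the NHPT, made outside the MANOVA, for example at T1 and adjusted for the T0 value. Fix the one hand score and the one visit before allocation is revealed to those analysing the data. Do not define the hand as the one that met the entry criterion, since no per-hand criterion is stated. Label ARAT and MAM-36 as secondary for aim 1, and report the other visit and the other hand as supportive estimates with confidence intervals.

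The change is to wording only, and the article reports that the trial had not begun. The cost is that ARAT, MAM-36 and the other visit can no longer carry the primary claim. T1 is one workable choice of visit; the essential step is to fix one in advance.

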#### Telerehab VR intervention

The telerehab VR intervention consists of a custom-made software program, that will run on a personal computer (or tablet), developed under Unity (Unity Technologies Inc., San Francisco, USA). Unity is a cross-platform game engine worldwide adopted to create three-dimensional, two-dimensional, virtual reality, and augmented reality games, as well as simulations and other experiences. PwMS will be requested to perform several ADLs from the three main areas of self-care, dressing, and meal preparation. Taking place in a realistic home scenario, the PwMS will pick up objects and move them to a predefined target clearly indicated on the screen. Hand and object trajectory are controlled by a low-cost non-contact infrared controller (Leap Motion). This instrument was proven successful in upper limb rehabilitation of individuals with neurologic and orthopedic conditions [33–35].

During the exercise, the hand coordinates will be continuously recorded; thus, data kinematic data calculated on the basis of the 3D trajectory like speed, accuracy on target placement, and movement smoothness will be accessible. This data will be stored in the PC/tablet and will also be sent remotely to the clinical center for further analysis/processing. Both target position and task complexity will define the exercise difficulty, which can be modified (i.e., increased or decreased) automatically on the basis of the previous performance or manually modified by the user. A suitable period of familiarization with the installation/management of the hardware and software will be carried out under the supervision of engineers and therapists to ensure that the exercises are being correctly performed. A schematic representation of the system is shown in Fig. 3.

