##### Adherence and user satisfaction

Adherence to exercise will be evaluated at the end of the intervention phase by examining the patient’s exercise diaries. The User Satisfaction Evaluation Questionnaire (USEQ) will be used to assess the participants’ satisfaction with the training program [39]. The USEQ is a reliable questionnaire with internal consistency designed to evaluate the satisfaction of the user in virtual rehabilitation systems.

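### Adherence and satisfaction are assigned a Condition × Time MANOVA, but adherence is evaluated only once and neither outcome can exist at T0

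*Protocol article*

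**What the plan says.** The Statistical analysis section of the protocol article names one method for all efficacy outcomes and includes these two: "adherence and user satisfaction (aim 3) will be examined using the Condition × Time mixed model multivariate analysis of variance (MANOVA". The factors are defined there as well: "Conditions will be a between-subjects factor and time and a within-subjects factor". The same section replaces missing data by multiple imputation.

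Under Outcomes, the heading that covers adherence and satisfaction reads "Secondary outcomes (collected at T0, T1, T2". The subsection on them says "Adherence to exercise will be evaluated at the end of the intervention phase by examining the patient’s exercise diaries". Satisfaction with the training program is measured with the USEQ, described as "designed to evaluate the satisfaction of the user in virtual rehabilitation systems". No time point of its own is given for the USEQ, and its use is not restricted to the VR arm.

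The Background section states the hypothesis that depends on the adherence comparison: "performing the telerehab VR training will lead to better outcomes in quality of life and adherence to upper limb exercise". Adherence and satisfaction are also a named secondary aim.

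**The concern.** A Condition × Time model asks whether change over repeated measurements differs between arms. It needs at least two measurements of the same quantity. Adherence to an 8-week program is a single total known when the program ends. There is no baseline adherence, and no study training takes place between T1 and T2 to adhere to. Satisfaction with a program likewise cannot be rated before the program starts.

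At stake is the stated hypothesis of better adherence with VR: the interaction that the plan names cannot address it. There is also a practical risk. An analyst who follows the heading and the imputation rule to the letter would find empty T0 and T2 cells and fill them.

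A second, smaller concern is the instrument. On the article's own description, the USEQ was built for users of virtual rehabilitation systems, yet its scores are to be compared with those of patients who receive one-on-one conventional therapy.

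**Working it through.** The plan gives no figure for these two outcomes that could be reproduced. Its sample-size statement concerns the NHPT and is not used here beyond the group sizes.

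**Inputs**
- G = 2 arms, N = 24, 12 per arm (Sample size).
- 8 weeks × 2 sessions per week = 16 sessions (Methodology and work plan; the Abstract also gives 16).
- T0 is about one week before the program, T1 about one week after it, and T2 one month after it, with only usual activities between T1 and T2 (Methodology and work plan).
- Adherence: one evaluation, at the end of the intervention. USEQ: no time point of its own.

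**Step 1: degrees of freedom, before covariates**

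Time: T − 1. Condition × Time: (G − 1)(T − 1). Within-subject error: (N − G)(T − 1). Condition: G − 1 on N − G.

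| Occasions T | Time | Condition × Time | Within error | Condition |
|---|---|---|---|---|
| 3 (as the heading says) | 2 | 2 | 22 × 2 = 44 | 1 on 22 |
| 2 (T1 and T2) | 1 | 1 | 22 × 1 = 22 | 1 on 22 |
| 1 (adherence as described) | 0 | 0 | 0 | 1 on 22 |

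For adherence T = 1, so the interaction has neither a numerator nor an error term. For satisfaction T can be at most 2.

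**Step 2: what literal use of the heading and the imputation rule would do**

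Three visits for 24 participants give 72 cells per outcome. For adherence, T0 and T2 are structurally empty: 48 of 72 (67%). For satisfaction, T0 is: 24 of 72 (33%). These values are not missing, because they were never defined, so imputation has no target. The Condition main effect would not escape this. In a three-visit layout it averages over the visits, so for adherence two of the three values averaged would be invented.

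**Step 3: what a single comparison can show**

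A two-group comparison at one time point is F(1, 22). With a two-sided 5% level and 80% power, the normal approximation gives a detectable difference of (1.96 + 0.84) × √(2/12) ≈ 1.14 SD. The t-based calculation gives about 1.20 SD. Only a large difference is detectable, so an estimate with its interval is more informative than a test alone.

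**Step 4: is the timing merely loose wording?**

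The Outcomes section marks exceptions in the headings of two other measures: impression of change (T1 only) and the BRB-N (T0 only). Adherence and satisfaction carry no such mark. The section therefore contradicts itself on adherence, and the analysis section follows the general heading.

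**The case against.** The strongest reply is that the usable contrast survives. The analysis section also provides for main effects, univariate F-ratios and Cohen's d. With one occasion the model collapses to the Condition effect, F(1, 22), which is essentially the right comparison. This stands in part. A reader might infer that adherence has no valid test at all, and the article does not support that. But the article names the Condition × Time model and does not say that it reduces to a single comparison for this outcome. Nor can the matter be put down to condensation in a journal article, since the method is stated and does not fit.

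Four other stronger readings are tempting and should not be drawn.

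- *Satisfaction is also measured only once.* The article does not say so. The USEQ could be given at T1 and T2, where the interaction would be F(1, 22). Only T0 is ruled out.
- *Patient diaries bias adherence towards VR.* The settings differ: clinic sessions are one-on-one with a therapist, and home sessions are not observed in the same way. But the article does not say how diaries are kept or checked in either arm. It also says of the VR movement data that "This data will be stored in the PC/tablet and will also be sent remotely to the clinical center", which might allow a check. Against that, the Discussion lists remote transmission as still to be implemented and concedes that the system cannot guarantee who trained. Clinic attendance records are not mentioned. Neither the size nor the direction of any bias follows.
- *The USEQ is meaningless for conventional therapy.* Its items are not shown. The described purpose raises a fair doubt about the between-arm comparison and does not prove the instrument unusable.
- *The NHPT analysis is spoiled.* That would follow only if all outcomes entered one joint MANOVA. The article does not say so, and its labelling of outcomes by aim is compatible with separate models.

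**Conclusion.** The point holds for timing against model. For adherence, the Time and Condition × Time terms have 0 degrees of freedom, so the planned interaction cannot test the adherence hypothesis. For satisfaction, a T0 value cannot exist, which contradicts the heading. Literal imputation would fill up to 48 of 72 adherence cells and 24 of 72 satisfaction cells with undefined values; this assumes that the heading and the imputation rule are applied as written. The doubt about the USEQ rests on the article's description of its purpose and remains a concern until its wording is seen.

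Severity is moderate. Secondary outcomes of a 24-person pilot are affected, the data needed for a correct adherence comparison can still be collected, and the primary outcome is untouched if it is modelled separately.

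**What to change.** 1. Take adherence and user satisfaction out of the Condition × Time MANOVA, and state that multiple imputation applies only to visits at which an outcome is scheduled.
2. Define adherence as sessions completed out of 16. Compare the arms once, at the end of the intervention, as a difference with a 95% confidence interval.
3. Correct the timing under Outcomes: adherence at the end of the intervention only, and satisfaction after the program only, with the visit or visits named.
4. Report the USEQ descriptively in the VR arm unless its wording is shown to suit both arms. Base any between-arm satisfaction comparison on a treatment-neutral item.
5. Where such data are available, cross-check diaries against the VR system's recorded data and clinic attendance. This would not show who performed a home session.

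Items 1 to 3 cost only wording. Item 4 adds one question at T1. Item 5 depends on what each center and the system actually record. The article reports that the trial had not begun, so on that account the changes could precede any data.

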## Discussion

The TEAMS project has tremendous potential to improve the quality of evidence and informed decisions of functional upper limb activities in PwMS. The project addresses the needs of PwMS [2, 6, 8], specifically, if they are provided access to functional upper limb exercises and does the location where the exercises are performed impact their outcomes? Is it necessary to travel to a healthcare facility with access to equipment and MS experts in order to benefit from upper limb exercises or can the PwMS safely and effectively exercise in their own home, if provided with expert guidance? We will compare a conventional healthcare facility training program with a VR telerehab home-based program. This information will impact the PwMS’s informed decisions as to how to spend their time and potentially limited resources.

If comparable results are found between the treatments in improving upper limb outcomes, this would suggest that PwMS can choose the program that best meets their personal needs, e.g., financial concerns, transportation, or accessibility issues. Secondly, this information can be used by healthcare providers and medical professionals by developing upper limb exercise programs that will most likely succeed and can then be distributed to neurologists and other medical providers. Finally, increasing an individuals’ accessibility to upper limb exercise options may prevent or slow the decline of disability, increase independence in ADL functions, and help maintain a better quality of life.

The telerehab VR proposal for restoring upper limb functional activities in PwMS is an expansion of a project originally developed by the University of Cagliari (Italy) that included a feasibility study which produced encouraging results. The following goals were reached during the initial phase: (1) recruitment of technological developers and MS professionals, (2) definition of upper limb functional difficulties and relevant rehabilitation exercises of the population target, and (3) development of a hardware-software VR platform based on low-cost tools, encouraging self-practice of functional exercises of the upper limb. Important elements include a user-friendly system that can be easily assembled, used in the home and be monitored from a distance by a medical/rehab professional.

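### The plan hypothesises no difference and sizes for non-inferiority, but analyses the NHPT only with tests of equality and sets no margin, interval or criterion for calling the programmes comparable

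*Protocol article*

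**What the plan says.** Four parts of the protocol article bear on this.

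- **Background (hypotheses).** "We hypothesize that there will be no difference in outcomes between a home-based telerehab VR training program" and the conventional clinic-based one, both after the intervention and 1 month later. A secondary hypothesis expects VR to do better on quality of life and adherence.
- **Sample size.** The trial is sized "assuming non-inferiority with moderate correlations among covariates" (R-squared 0.50), with 80% power and alpha 5%. The same sentence says that "24 subjects (12 in each group) will be required in order to detect differences between the two treatment groups". The paragraph also notes that "a 20% change in the NHPT demonstrates a clinically meaningful worsening in PwMS", but does not call this a margin. The number 12 per group is a pilot rule of thumb.
- **Statistical analysis.** The outcomes, NHPT included, "will be examined using the Condition × Time mixed model multivariate analysis of variance (MANOVA) followed by an inspection of the univariate F-ratios". Post hoc analyses with corrected alpha follow, and effect sizes are given as eta-squared and Cohen's d. No confidence interval is mentioned.
- **Discussion (and the Abstract).** "If comparable results are found between the treatments in improving upper limb outcomes, this would suggest that PwMS can choose the program" that suits them. Neither place says what would count as comparable.

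**The concern.** A test whose null is equality can give evidence that two programmes differ. It cannot give evidence that they are alike, because a non-significant F-ratio arises from true similarity and from imprecision alike. Here equality is the investigators' own hypothesis, so the smaller and noisier the trial, the more often its result would be consistent with that hypothesis.

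At stake is the main practical message, that patients may pick a programme on cost, transport or access. With no stated criterion, that message could rest on low power.

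This is not a detail left to an unseen analysis plan. The article names the method for its primary outcome, and that method does not answer the question posed in the Background.

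**Working it through.** **1. The plan's own figure.** As a rule of thumb, 2 × 12 = 24. As a power calculation it cannot be reproduced, because neither a margin nor an SD is given. Solving backwards (normal approximation, two-sided 5% or one-sided 2.5%, 80% power), the margin or difference that 12 per arm can address is

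(1.960 + 0.842) × √(2/12) × √(1 − 0.50) = 2.802 × 0.408 × 0.707 = 0.81 SD (0.85 with the noncentral t).

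If 20% of the mean were the margin and the SD were 0.25 of the mean, the number per arm would be

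2 × 2.802² × (0.25² × 0.50) / 0.20² = 12.3, rounded up to 13 (26 in total).

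That is close to 24, but the article states neither of those two inputs.

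**2. How often a real deficit would go undetected.**

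- From the article: 12 per arm, R-squared 0.50, alpha 5%, and a 20% NHPT change as meaningful worsening.
- Assumed: a two-sided test; a single comparison at T1 with one covariate degree of freedom (df = 21), standing in for the planned model; SD/mean from 0.20 to 0.50.

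Standard error (SE) as a fraction of the mean = (SD/mean) × √0.50 × √(2/12). Noncentrality = 0.20 / SE. The critical value is t(0.975; 21) = 2.080, and the 95% half-width is 2.080 × SE.

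| SD/mean | SE | Noncentrality | Non-significant despite a true 20% deficit | 95% half-width (% of mean) |
|---|---|---|---|---|
| 0.20 | 0.058 | 3.46 | 9% | 12% |
| 0.25 | 0.072 | 2.77 | 25% | 15% |
| 0.30 | 0.087 | 2.31 | 40% | 18% |
| 0.40 | 0.115 | 1.73 | 62% | 24% |
| 0.50 | 0.144 | 1.39 | 74% | 30% |

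If the covariates explained nothing (R-squared 0, df = 22), the fourth column would read 35%, 53%, 65%, 78% and 85%.

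**3. Comparison with a proper test.** A non-inferiority test with a 20% margin would wrongly accept a true 20% deficit in 2.5% of trials (one-sided 2.5%) or 5% (one-sided 5%). Reading non-significance as comparability does worse than either, even at the most favourable SD in the table.

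**4. What an interval would show.** At SD/mean 0.30, an observed VR deficit of 10% would be non-significant. Its 95% interval would be 10 ± 18, that is from −8% to +28%, which includes deficits beyond 20%.

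**5. What 12 per arm can deliver.** With no true difference, a 20% margin, one-sided 2.5% and R-squared 0.50, the power to conclude non-inferiority is 91%, 75%, 60%, 38% or 26% for the five SDs in the table.

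**The case against.** The strongest reply is that this is a pilot. It is labelled so, its size follows a pilot rule of thumb, and one stated aim is to generate effect sizes for a larger trial. That defends the choice of 24 patients. It does not defend the conclusion: the primary goal is to compare effectiveness, the Sample size section claims 80% power, and the Discussion draws a message for patients.

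Several stronger readings are tempting, and the article does not support them.

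- A reader might infer that the F-ratios are the only output and give no directional estimate. Post hoc contrasts and Cohen's d are planned, so signed, time-specific estimates can be obtained. What is missing is an interval and a criterion.
- A reader might infer that two programmes that both fail would be called comparable. The conclusion is conditioned on results in improving upper limb outcomes, and Time is a factor in the model. The lack of an untreated arm limits attribution, but the conclusion is not indifferent to non-improvement.
- A reader might infer that the plan defines comparable as p > 0.05. It does not. It gives no definition at all, and significance tests are the only decision tool on offer.
- A reader might treat the hypothesis as plainly one of non-inferiority. That word occurs only in the sample size parenthesis. No difference is nearer to equivalence, which needs both limits.
- A reader might infer that intent-to-treat analysis will pull the arms together here. The article gives no expected non-adherence, so this remains a general caution.

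It is also fair to say that the size of the problem depends on an SD that the article does not give, and that it is modest at SD/mean 0.20.

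**Conclusion.** The concern holds as a mismatch between hypothesis, sizing and analysis, together with a missing decision criterion. Whichever of equivalence or non-inferiority is meant, a non-significant F-ratio or post hoc test establishes neither, and effect sizes without intervals do not close the gap.

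The chance of missing a true 20% NHPT deficit runs from about 9% to 74% over SD/mean 0.20 to 0.50. These figures rest on assumed SDs, on the article's R-squared of 0.50, and on a single T1 comparison in place of the planned repeated-measures model with cognitive covariates. Correcting alpha post hoc would make non-significance more likely for any one contrast. The 20% is used as the article's own benchmark of meaningful worsening, not as a margin that it has adopted.

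The point does not show that 24 patients are too few for a pilot. The F-tests remain suitable for the secondary hypotheses that VR does better on quality of life and adherence. Because the main conclusion depends on it, the mismatch should be settled before the data are analysed.

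**What to change.** First, state whether the aim is equivalence or non-inferiority, and make the Background, Sample size and Statistical analysis sections agree. Then take one of two routes.

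1. **Keep the comparative claim.** Report the baseline-adjusted VR-minus-conventional difference (or ratio) in NHPT at T1 and T2, each with a confidence interval. Fix the interval's level in advance, since the article does not say whether alpha is one- or two-sided. Conclude non-inferiority only if the limit on the side of VR being worse lies inside a pre-stated, justified margin; for equivalence, both limits must. The margin should be no wider than the 20% that the plan calls a meaningful worsening. Otherwise report the result as inconclusive.
2. **Treat it as a pilot throughout.** Drop the non-inferiority assumption and the comparability conclusion, and report the estimate with its interval as input to the larger trial.

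Under either route, keep the F-tests for quality of life and adherence.

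The cost is revised wording and, for the first route, one additional model. No new data are needed, and the article states that the trial had not begun. The drawback of the first route is that, with 24 patients, the verdict will often be inconclusive.
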